#### **4.2.5 Telesurgery monitoring data**

To characterize the status of the telesurgery system, the following data will be collected:

1. Round-trip network latency (for telesurgery): The round-trip network latency is defined as the time latency of data packages between transmission and reception.
2. Display latency (for telesurgery): The display latency is defined as the time latency between coding and encoding the endoscope image.
3. Frame loss (for telesurgery): The frame loss is defined as the loss of data packages during data transmission.
4. Malfunction: The malfunction of the local surgical robot or telesurgery system will be recorded. The local surgical robot or telesurgery system is tested systemically one day preoperatively. A malfunction of the telesurgery system is defined as the system being out of control for any reason, such as a telecommunications pathway fault, a laboratory pathway fault, or a robotic fault. A malfunction of the local surgical robot

is defined as the robot being out of control for any reason.

## **5. Definitions**

### **5.1 Success of the surgery**

The success was defined as the surgery being completed effectively as planned, without conversion to other surgical types and significant side injury or delays due to system malfunctions. Telesurgery was considered successful if it could be completed only using the telesurgery system without conversion to local surgery for any reason.

### **5.2 Serious adverse events**

A serious adverse event is defined as any adverse event that results in death, is life-threatening, or results in any side injury to the participant during the surgery due to a malfunction of the telesurgery system.

### **5.3 Malfunction of the surgery system**

The malfunction of the telesurgery system is defined as the system being out of control for any reason, such as a telecommunications pathway fault, a laboratory pathway fault, or a robotic fault. A malfunction of the local surgical robot is defined as the robot being out of control for any reason.

## **6. Analysis population**

### **6.1 Intention-to-treat (ITT) Analysis Set**

The ITT population includes all randomized participants of this trial.

Missing data of the primary outcome were imputed by Multiple Imputation (e.g., fully conditional specification). Unless otherwise specified, other missing data will not be interpolated.

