### **3.6 Trial Assessments**

Trial assessments will be conducted at certain time intervals (defined around the date of surgery):

- (1) Baseline:** Data will be recorded before the surgery.
- (2) Perioperative:** Operative details, task load of the medical team, and status monitoring data of the telesurgery system, including the operation

details, obvious side injury, and surgery video, and monitoring data of the telesurgery system, will be collected immediately after the surgery.

**(3) In-hospital postoperative:** The time to hospital discharge, length of days in critical care, reoperation intervention in the hospital, and blood transfusion rates will be recorded according to the clinical information system of each site.

**(4) Four and six weeks after the surgery:** The complications, tests, and questionnaires will be recorded or measured at 4 and 6 postoperatively. Further follow-up will continue to be performed at longer time points, including 12 weeks, 24 weeks, and 48 weeks.

**The time point of the primary outcome is the finishing time of the surgery.** The completion of surgery is defined as all the planned steps of the operation being finished without any conversion or obvious side injury. After the surgery, the blood loss, surgical approach, and any other surgical details will be recorded by the medical team.

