### 3.2 Sample Size

According to the requirements of the "Guideline for the Design of Clinical Trials of Medical Devices" (published by CFDA), the number of trial cases was inferred based on the non-inferiority sample size

calculation method, and the number of cases was calculated through joint discussion by clinical trial institutions, major researchers, and statistical analysts.

The formula is as follows:

$$n_T = n_C = \frac{(Z_{1-\alpha/2} + Z_{1-\beta})^2 [P_C(1-P_C) + P_T(1-P_T)]}{(|D| - \Delta)^2},$$

where  $\alpha = 0.025$  (one-sided),  $\beta = 0.2$  (80% confidence), and the non-inferiority margin  $\Delta = 10\%$ . Assuming that the surgical success rate of the experimental group and the control group is equal, the expected surgical success rate of the two groups is 98% (i.e.,  $P_T = P_C = 98\%$ ). As the ratio between the two groups is 1:1, 31 subjects are needed in each group. Considering that the dropout rate of subjects during the trial is about 10% or more, this study plans to enroll 68 subjects, with 34 in the experimental group and 34 in the control group. If the dropout rate exceeds the expected 10%, resulting in insufficient valid data, the number of patients enrolled can be appropriately increased, and the proposed increase in the number of patients enrolled should be filed with the Ethics Committee of Chinese PLA General Hospital.

Urologic surgery is divided into upper and lower urinary tract surgeries. In this clinical trial, representative surgical methods of partial

nephrectomy and prostatectomy are selected for surgery. In the end, partial nephrectomy and prostatectomy in this scheme is no less than 30%, and each clinical center ensures that subjects are operated on for both partial nephrectomy and prostatectomy surgery. This information will be summarized after the end of the trial. According to the non-inferiority test, when the lower limit of the 95% confidence interval of the difference in surgical success rate between the two groups is  $> -10\%$ , the non-inferiority hypothesis is established, which can be considered to meet the qualified requirements of this clinical trial.

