## **4 Outcomes**

### **4.1 Primary outcome:**

The primary objective of this clinical trial will be to evaluate and validate the safety and efficacy of the telesurgery system in urologic surgery and compare it to local urologic surgery. The success was defined as the surgery being completed effectively as planned, without conversion to other surgical types and significant side injury or delays due to system malfunctions. Telesurgery was considered successful if it could be completed only using the telesurgery system without conversion to local surgery for any reason. The success or failure of each surgery will be jointly confirmed by the remote and local medical teams together.

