## **6.2 Per-Protocol Analysis Set (PPS)**

The PPS population consists of all randomized participants who received surgery, including telesurgery and normal local surgery.

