## **8.3 Efficacy analysis**

### **8.3.1 Primary outcome analysis**

The primary outcome will be analyzed by a non-inferiority analysis. According to the medical statistics scenario, the main efficacy evaluation is based on the intention-to-treat population set and per-protocol population set. The statistical description and inference will be based on the characteristics of the data, and the appropriate descriptive indicators and hypothesis testing methods will be selected.

The primary efficacy indicator of surgical success rate uses a non-inferiority test, with the following hypotheses tested:

Null hypothesis:  $H_0: PT - PC \leq -\Delta$ ;

Alternative hypothesis:  $H_1: PT - PC > -\Delta$ .

At  $\alpha = 0.025$  (one-sided test) and  $\beta = 0.2$  levels, the success rates of the two groups will be statistically described and compared, and the 95% confidence interval (CI) of the difference in success rates between the two groups will be calculated. If the lower limit of the 95% CI of the difference in success rates between the two groups is greater than the non-inferiority margin ( $-\Delta$ ), it can be concluded that the experimental group is non-inferior to the control group.

The difference in the primary outcome (success rate) between the telesurgery and local surgery groups will be compared using the Miettinen-Nurminen method or Newcombe-Wilson score method test, according to the success rate data. The tipping assay can be used to determine the robustness and sensitivity the statistical conclusion.

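### Multiple imputation of the primary outcome mainly fills in operations that were not done; count system-related non-delivery as failure and make a tipping table mandatory

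*Combined protocol and SAP*

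**What the plan says.** SAP 6.1 defines the set: "The ITT population includes all randomized participants of this trial". It then gives the only rule for a missing primary outcome: "Missing data of the primary outcome were imputed by Multiple Imputation (e.g., fully conditional specification"). It gives no model, covariates, number of imputations or pooling rule. The SAP contents page lists a section 8.4 on loss to follow-up and other missing data, but in the body 8.4 is adverse event reporting.

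Protocol 3.6 fixes when the outcome is known: "The time point of the primary outcome is the finishing time of the surgery". The table of assessments (protocol section 5) puts randomisation at the screening visit, day -7 to 0. SAP 4.2.5 adds: "The local surgical robot or telesurgery system is tested systemically one day preoperatively".

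SAP 4.1 (repeated in 5.1 and in protocol 2.1) defines success in the experimental arm: "Telesurgery was considered successful if it could be completed only using the telesurgery system without conversion to local surgery for any reason".

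SAP 8.3.1 bases the main evaluation on both the ITT and per-protocol sets, with a Miettinen-Nurminen or Newcombe-Wilson interval. On sensitivity it says: "The tipping assay can be used to determine the robustness and sensitivity the statistical conclusion". For the per-protocol set, SAP 6.2 says: "The PPS population consists of all randomized participants who received surgery".

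**The concern.** Imputation suits an outcome that exists but was not seen. Here later dropout cannot make the outcome missing. An unrecorded result is possible but unlikely, because both teams jointly confirm each one. What remains is a participant randomised up to a week before surgery who was never operated on.

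Some of those cancellations could be failures to deliver telesurgery, for example a fault found at the test the day before. The SAP does not say how such a participant counts. If the outcome is treated as missing, the imputed value comes from operated participants and is nearly always a success. Whether telesurgery can be delivered as planned is what the trial is meant to measure.

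The choice of rule also matters more than usual. The margin is 10 points and each arm has 34 participants, so one participant is worth 1/34 = 2.9 points.

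**Working it through.** **Inputs.** SAP 3.2: "the expected surgical success rate of the two groups is 98"%; margin 10 points; one-sided alpha 0.025; power 80%; 31 per arm needed and 34 per arm enrolled, allowing about 10% dropout. The documents do not say how many will go without an operation. I assume 3 of 34 in an arm, which is the whole planned loss (34 - 31).

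**The plan's own figure.** (1.960 + 0.842)² × (2 × 0.98 × 0.02) / 0.10² = 30.77, so 31 per arm. This reproduces.

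**Interval.** The Miettinen-Nurminen lower limit L solves (difference - L) / √{[p̃T(1-p̃T)/nT + p̃C(1-p̃C)/nC] × N/(N-1)} = 1.96, where the p̃ are the maximum likelihood rates constrained to differ by L. If every local operation succeeds and the arms are equal at n, the constrained local rate is 1. With δ = -L, a = 1.96² × [N/(N-1)] / n, and d the shortfall in the telesurgery rate, this becomes (δ - d)² = a δ(1-δ). With d = 0, δ = a/(1+a).

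**No failures, 34 per arm.** a = 3.8415 × (68/67) / 34 = 0.1147, so δ = 0.1147/1.1147 = 0.103. The limit is -10.3%, which fails. The Newcombe limit is 34/(34 + 3.84) - 1 = -10.15%, which also fails.

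**Three telesurgery operations not started, counted as failures.** d = 3/34 = 0.0882. Solving (δ - 0.0882)² = 0.1147 δ(1-δ) gives δ = 0.231, a limit of -23.1%.

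| Three not operated on; all observed operations succeed | Operated only | Imputed as success | Counted as failure |
|---|---|---|---|
| Telesurgery arm only | 31/31 v 34/34: -11.2% | 34/34 v 34/34: -10.3% | 31/34 v 34/34: -23.1% |
| Both arms | 31/31 v 31/31: -11.2% | 34/34 v 34/34: -10.3% | 31/34 v 31/34: -15.7% |
| Local arm only | not computed | 34/34 v 34/34: -10.3% | 34/34 v 31/34: -1.9% |

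Nothing in the first two rows clears -10%. The last row shows that a blanket rule of no operation = failure can favour telesurgery.

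**When the rule changes the decision at 34 per arm.** Suppose one local operation fails and three telesurgery operations are not started. Imputed as successes, 34/34 v 33/34 gives -7.5% and passes. Counted as failures, 31/34 v 33/34 fails, since even 31/34 v 30/34, a kinder result for telesurgery, gives -13.2%.

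**Probability of declaring non-inferiority** (exact binomial, true success 98% among those operated on in each arm). With three not operated on in telesurgery only: 0.276 on those operated on, 0.316 imputed as success, below 0.001 counted as failure. With three in the local arm only: 0.279 on those operated on, 0.908 counted as failure.

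**Can the model be fitted?** Expected failures per arm are 34 × 0.02 = 0.68. P(none in one arm) = 0.98^34 = 0.503; P(none in both) = 0.98^68 = 0.253. With no failures in an arm, a logistic model containing arm has no finite estimate, and the draws depend on whatever prior or penalty the software applies.

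**How far unstated choices move the result.** Take 31/31 observed and 3 missing in each arm. If every draw is a success, the Newcombe limit is -10.15%. With beta-posterior draws (prior parameters 0.01 to 0.5), 20,000 imputations and a pooled Wilson-type interval, it is -18.7% to -19.1%. The number of imputations matters too. With prior parameters 0.5, one imputed dataset contains no failure with probability [(31.5/32)(32.5/33)(33.5/34)]² = 0.912, and five contain none with probability 0.912^5 = 0.63. The same data can therefore give about -10% or about -19%.

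**The case against.** The strongest reply is that the main failure route is not missing data. A participant assigned to telesurgery but operated on locally is already a failure under SAP 4.1 and 5.1, and protocol 3.4.2 and 12.1 direct malfunctions to the backup console or a local operation. That stands. Only participants with no operation, or no recorded result, reach imputation. It is unstated whether a switch before the first step is a conversion, and no text says that failing the test the day before leaves the outcome missing.

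A reader might infer that imputation always pushes toward non-inferiority. The documents do not support this. Arm-specific imputation leaves the point estimate essentially at its value among those operated on, proper pooling can widen the interval, and the direction depends on which arm has the losses. The push appears only against counting the cancelled operations as failures.

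A reader might also infer that imputation removes all between-imputation variance. That holds only if the success rate is fixed at 100%. With 33/33 observed and 3 missing per arm, 8% to 16% of properly imputed datasets contain an imputed failure (Jeffreys and uniform priors).

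With no observed failures, imputed successes alone reach a pass only in a larger trial. At 36 randomised and 33 operated on per arm, -10.6% becomes -9.8% if every draw is a success, and 36 would need the top-up clause in protocol 9.2.

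Finally, the per-protocol set is a co-main analysis and a tipping analysis is named. Neither closes the gap: the per-protocol set drops the same participants, and the tipping analysis is optional and undefined.

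**Conclusion.** The point holds as a gap in the primary analysis that should be closed. It does not show a general bias toward non-inferiority. The stated rule mainly supplies results for operations not done, can turn a system-related cancellation into a success, and cannot be carried out reproducibly in the situation the plan expects.

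With three telesurgery non-starts and no other failures, the choice of rule moves the lower limit by 23.1 - 10.3 = 12.8 points, more than the margin, though both results fail. With one local failure the same choice changes the decision.

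These sizes assume three participants not operated on, all in telesurgery and all for system reasons. If the planned 10% dropout falls mostly after surgery, few or no primary outcomes will be missing and the effect will be small.

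**What to change.** 1. Drop multiple imputation for the primary outcome from SAP 6.1.
2. In the ITT analysis, count as failure any assigned operation not started or not completed for a system, network, equipment or surgeon-side reason. Apply the same rule to robot-related cancellations in the local arm.
3. State in SAP 4.1 and 5.1 that conversion to local surgery includes a switch before the first step.
4. For participants not operated on for unrelated reasons (withdrawal, medical cancellation), analyse the observed outcomes.
5. Replace the optional tipping analysis with a mandatory table of the lower limit for every combination of missing outcomes, including telesurgery missing = failure with local missing = success. With three missing per arm that is 4 × 4 = 16 cells.
6. Record the reason for non-operation by arm.

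The cost is SAP wording, one CRF item and one table. The telesurgery result becomes slightly more conservative. Reasons must be classified by staff who know the allocation (protocol 3.3). If the table covers everyone not operated on, whatever the recorded reason, its worst-case cell bounds the effect of that judgement.

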## **6.2 Per-Protocol Analysis Set (PPS)**

The PPS population consists of all randomized participants who received surgery, including telesurgery and normal local surgery.

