## **7 ELIGIBILITY CRITERIA**

### **7.1 Inclusion Criteria**

Participants will have to meet the following criteria for inclusion in the study: (1) age, 18–80 years; (2) body mass index, 18–30 kg/m^2; (3) fit to undergo urologic laparoscopic surgery, including prostatectomy and partial nephrectomy; (4) physiological condition suitable for robot-assisted laparoscopic surgery; (5) willingness to cooperate and complete study follow-up and related examinations.

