### 9.2 Sample Size Determination

According to the requirements of the "Guideline for the Design of Clinical Trials of Medical Devices" (published by CFDA), the number of trial cases was inferred based on the non-inferiority sample size calculation method, and the number of cases was calculated through joint discussion by clinical trial institutions, major researchers, and statistical analysts.

The formula is as follows:

$$n_T = n_C = \frac{(Z_{1-\alpha/2} + Z_{1-\beta})^2 [P_C(1-P_C) + P_T(1-P_T)]}{(|D| - \Delta)^2},$$

where  $\alpha = 0.025$  (one-sided),  $\beta = 0.2$  (80% confidence), and the non-inferiority margin  $\Delta = 10\%$ . Assuming that the surgical success rate of the experimental group and the control group is equal, the expected surgical success rate of the two groups is 98% (i.e.,  $P_T = P_C = 98\%$ ). As the ratio between the two groups is 1:1, 31 subjects are needed in each group.

Considering that the dropout rate of subjects during the trial is about 10% or more, this study plans to enroll 68 subjects, with 34 in the experimental group and 34 in the control group. If the dropout rate exceeds the expected 10%, resulting in insufficient valid cases, the number of participants can be appropriately increased, and the number of the total valid cases should not be higher than 34 of each trial group. The increase in the number of patients enrolled should be filed with the Ethics Committee of Chinese PLA General Hospital.

Urologic surgery is divided into upper and lower urinary tract surgeries. In this clinical trial, representative surgical methods of partial nephrectomy and prostatectomy are selected for surgery. In the end, partial nephrectomy and prostatectomy in this scheme is no less than 30%, and each clinical center ensures that subjects are operated on for both partial nephrectomy and prostatectomy surgery. This information will be summarized after the end of the trial. According to the non-inferiority test, when the lower limit of the 95% confidence interval of the difference in surgical success rate between the two groups is  $> -10\%$ , the non-inferiority hypothesis is established, which can be considered to meet the qualified requirements of this clinical trial.

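### The SAP's per-protocol set is an all-operated set, so it cannot act as the per-protocol check in the non-inferiority evaluation, and no rule says which set decides if ITT and per-protocol results differ

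*Combined protocol and SAP*

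**What the plan says.** SAP 6.1 defines the first set: "The ITT population includes all randomized participants of this trial". It adds, "Missing data of the primary outcome were imputed by Multiple Imputation".

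SAP 6.2 defines the second set, and this sentence is the whole definition: "The PPS population consists of all randomized participants who received surgery, including telesurgery and normal local surgery".

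SAP 8.3.1 gives both sets a confirmatory role: "the main efficacy evaluation is based on the intention-to-treat population set and per-protocol population set". It then states a single criterion, that the lower 95% limit of the difference in success rates must lie above -10%. It does not say whether one set or both must meet it.

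Three other places bear on the point:

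- Protocol 3.6 fixes the timing: "The time point of the primary outcome is the finishing time of the surgery".
- SAP 5.1 defines success in the telesurgery arm: "Telesurgery was considered successful if it could be completed only using the telesurgery system without conversion to local surgery for any reason".
- Protocol 7.1 and 7.2 list eligibility criteria. SAP 6.2 does not refer to them, and neither document defines a major protocol deviation.

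**The concern.** In a non-inferiority trial, patients who get the other arm's treatment, or who should not have been enrolled, can pull the arms together and make a worse treatment look acceptable. A per-protocol analysis is run beside ITT to expose this, which it can do only if its membership rule removes such patients. The rule in SAP 6.2 does not.

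Wrong-modality patients are foreseeable here. The table of assessments puts randomization between day -7 and day 0. The system is tested the day before surgery, and the link is set up before the patient enters the operating room. A patient can therefore be allocated to telesurgery and, after a failed check, be operated on locally from the start. Under SAP 6.2 that patient is in the per-protocol set. The SAP does not say how the case is scored, or whether the set is analysed as randomized or as treated.

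Agreement between two sets with nearly the same members would look like confirmation but would be largely built in. In the one situation where they can differ, the plan gives no rule for the conclusion.

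**Working it through.** **The plan's own figure.** Inputs from Protocol 9.2: success 98% in both arms, margin 10 points, one-sided alpha 0.025, power 80%.

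n = (1.960 + 0.842)² × (2 × 0.98 × 0.02) / 0.10² = 30.77, so 31 per arm, as stated. (This takes the first Z at 0.975.) The plan enrols 34 per arm to allow for dropout. The definition of the per-protocol set does not enter this calculation.

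**How far the two sets can differ.** ITT is everyone randomized, and the per-protocol set is everyone randomized and operated on. The difference is the unoperated patients. Protocol 9.2 assumes about 10% dropout or more. At 10%, all of it before surgery, 34 × 0.9 = 30.6 remain, so the sets differ by about 3 per arm. If every patient is operated on, they are identical.

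**What one wrong-modality patient does.** The Miettinen-Nurminen lower limit is the value δ below the observed difference that solves

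(p_T − p_C − δ) / √{[q_T(1 − q_T)/n_T + q_C(1 − q_C)/n_C] × N/(N − 1)} = 1.96,

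where p_T and p_C are the observed success rates, N = n_T + n_C, and q_T, q_C are the maximum-likelihood rates under q_T − q_C = δ. Suppose one telesurgery-arm patient was operated on locally from the start, and each arm is as follows:

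| Handling of that patient | Telesurgery | Local | Miettinen-Nurminen | Newcombe | Above -10%? |
|---|---|---|---|---|---|
| Kept, scored as success | 34/34 | 33/34 | -7.5% | -7.5% | yes |
| Kept, scored as failure | 33/34 | 33/34 | -12.5% | -12.2% | no |
| Excluded | 33/33 | 33/34 | -7.8% | -7.8% | yes |

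The first two rows differ by scoring, which would affect ITT and the per-protocol set alike, so that contrast does not measure the membership defect. Comparing row 1 with row 3, a corrected set leaves the conclusion unchanged. Comparing row 2 with row 3, it makes the per-protocol result more favourable.

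**Dilution, as an illustration.** Assumptions: true success 88% for telesurgery and 98% for local surgery (exactly at the margin), 34 per arm, and a fraction c of the telesurgery arm operated on locally. If those patients are scored as successes at 98%, the expected difference is 0.88(1 − c) + 0.98c − 0.98. If they are scored as failures, it is 0.88(1 − c) − 0.98. The chance of declaring non-inferiority comes from exact binomial enumeration and is the same with either interval method.

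| c | Difference, scored success | Chance of false claim | Difference, scored failure | Chance of false claim |
|---|---|---|---|---|
| 0 | -10.0 points | 1.6% | -10.0 points | 1.6% |
| 2/34 | -9.4 | 1.9% | -15.2 | 0.3% |
| 10% | -9.0 | 2.2% | -18.8 | 0.1% |
| 20% | -8.0 | 3.0% | -27.6 | under 0.1% |

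**The case against.** The strongest reply is that the definition does little harm. Four parts of it deserve an answer.

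- **Scoring.** SAP 5.1 leans towards counting never-started telesurgery as failure, since the operation was not completed with the telesurgery system alone. Keeping such a patient is then conservative, and removing the patient helps telesurgery. This stands, and it is why a new membership rule alone is not enough. It is incomplete because SAP 5.1 speaks of conversion, and an operation that never began remotely is not clearly a conversion.
- **Dilution is modest.** This also stands. Among the cases shown, the false-claim chance passes the nominal 2.5% only at 20% crossover with all crossovers scored as successes.
- **The set does some work.** A reader might infer that the per-protocol analysis adds no protection at all. That goes too far: unoperated patients have imputed outcomes in ITT, so the all-operated set is an observed-outcome check on the imputation. It is still not a check on crossover, eligibility or deviations.
- **Wording.** The closing phrase of SAP 6.2 may have been meant as surgery as allocated. It does not say so, and no other section supplies the condition.

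A reader might also infer that the plan lets the sponsor quote whichever set is favourable. SAP 8.3.1 names both sets, which naturally means that both are reported. What is missing is the rule for disagreement.

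**Conclusion.** The point holds as a defect of definition and of decision rule. The set in SAP 6.2 is an all-operated set, and for the primary outcome it departs from ITT only through unoperated patients (0 to about 3 per arm at 10% dropout). It cannot do the per-protocol job that SAP 8.3.1 relies on, and SAP 8.3.1 does not say which set decides.

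Confidence is high on the wording and low on the numerical consequence. The number of wrong-modality or ineligible patients is not in the documents, so the limits and false-claim chances above are illustrations. One might infer from the -7.5% and -12.5% limits that the membership rule alone can reverse the trial's conclusion in telesurgery's favour. It does not follow, because those figures differ by scoring, and excluding the patient gives -7.8%, which still meets the margin. The change should be made, but the sample size calculation is not affected.

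**What to change.** Three changes to the SAP, to be made together:

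1. **SAP 6.2.** Define the per-protocol set as randomized participants who met the eligibility criteria, whose operation was started with the allocated modality, and who had no major deviation from a list fixed before database lock. State that conversion after the start keeps the patient in the set as a failure.
2. **SAP 8.3.1.** State that non-inferiority is claimed only if the lower 95% limit exceeds -10% in both ITT and the per-protocol set.
3. **SAP 5.1 and 6.1.** State that in ITT a telesurgery-arm patient whose operation was never started by telesurgery counts as a failure, in line with the existing definition of success.

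The second change must not be dropped. In the example, the first change alone moves the per-protocol limit from -12.5% to -7.8%. With the second and third, ITT stays at -12.5% and no claim is made.

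The cost is SAP wording and an agreed list of major deviations. The per-protocol set may lose a few patients, and requiring both sets makes the claim slightly stricter. The calculated 31 per arm does not change.
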